## Methods

### Study design and setting

This study will use a stepped wedge cluster randomised controlled trial design. This method is a form of randomised controlled trial where randomisation occurs while still allowing all participants the opportunity to undertake a period of intervention [12]. In this study, the randomisation will occur at a clinic level rather than individual participant level. Participants will be recruited from 15 community satellite hemodialysis clinics across five healthcare organisations in Melbourne, Australia. Each clinic will represent a cluster unit. The stepped wedge design will consist of three groups each containing five randomly allocated cluster units. The first group will receive 36 weeks of the AEP-coordinated exercise intervention, the second group will receive 24 weeks, and the third group will receive 12 weeks. The study will be conducted over a 48 week period, incorporating a 12 week pre-intervention period. The study design was reviewed by the Australian New Zealand Clinical Trials Registry (ANZCTR), approved and registered as ACTRN12612001223820 on the 19th November, 2012.

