### Randomization

An individual not associated with the trial will perform the randomization using the Microsoft Office Excel™ computer-generated random number system. Each cluster (each dialysis clinic) will be randomly prescribed a number and the five clinics with the 5 lowest numbers will be designated into Group 1 (receiving 36 weeks of the exercise intervention), numbers 6–10 will be allocated to Group 2 (receiving 24 weeks of the exercise intervention) and the final 5 clinics will be allocated to Group 3 (receiving 12 weeks of the exercise intervention). Allocation will be concealed at the time of participant consent; however the participants and clinic staff will be made aware of their group at the commencement of the intervention. Blinding of intervention group number to clinical staff and dialysis patient participants will not be possible once the intervention commences.

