### Data collection

Baseline data (Time 1) for all participants will be collected 12 weeks prior to the commencement of the intervention for the first group. The second round of data collection (Time 2) will be conducted 12 weeks later and participants from the five clinics randomised to receive 36 weeks of intervention (Group 1) will commence the exercise intervention. The third round of data collection (Time 3) will be conducted 12 weeks later and participants from the five clinics randomised to receive 24 weeks of intervention (Group 2) will commence the exercise intervention. The fourth round of data collection (Time 4) will be conducted 12 weeks later and participants from the five clinics randomised to receive 12 weeks of intervention (Group 3) will commence the exercise intervention. The final round of data collection will be conducted in the week after the intervention ceases in all clinics, 48 weeks after the first data is collected (Time 5) (Table 1).

**Table 1 T1:** Outcome measures

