### Primary outcome measure

Objective physical function is the primary outcome measure in this study and will be measured using the 30-second sit to stand test. The test will follow the protocols developed by Rikli and Jones [13] and Dite and Temple [14], and is a simple, non-invasive test that can be conducted with minimal equipment in the hemodialysis clinic. The 30-second sit to stand test has been validated for use with older people and people with chronic disease [13,14]. Tests will be conducted before participant’s midweek hemodialysis treatment every 12 weeks from the start date by an AEP who is blinded to the intervention group.

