### Statistical analyses

For the primary outcome measure there will be five data collection points, one every 12 weeks as follows: Time 1 (0 weeks, no intervention), Time 2 (12 weeks, Group 1 commences intervention), Time 3 (24 weeks, Group 2 commences intervention), Time 4 (36 weeks, Group 3 commences intervention) and Time 5 (48 weeks, intervention completed). This design characteristic means analyses will occur at three time points (Time 3 to Time 5) with the data at each of these time points compared with baseline data. Three tests means that the standard α value (p < 0.05) will need to be divided by three (a Bonferroni adjustment): α = .05/3 = .0167. Initially, analyses of variance with baseline scores as co-variates (ANCOVAs) will be the method of analysis. In addition, to account for the clustering effect, generalised linear mixed models with random effects will be used to analyse differences between control period and intervention period.

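### The ANCOVAs adjust for Time 1 alone, although Time 2 is a second, later measurement scheduled before any clinic is exposed: a modest loss of efficiency, confined to the ANCOVAs

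*Protocol article*

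**What the plan says.** The Data collection section of the protocol article ties the word baseline to one visit: "Baseline data (Time 1) for all participants will be collected 12 weeks prior to the commencement of the intervention for the first group". The Statistical analyses section then says that "analyses will occur at three time points (Time 3 to Time 5) with the data at each of these time points compared with baseline data", and that initially "analyses of variance with baseline scores as co-variates (ANCOVAs) will be the method of analysis". It never says in so many words that Time 1 is the only covariate. That follows from reading the two sections together, since the article gives no other meaning of baseline.

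The same section gives the position of the second visit: "Time 2 (12 weeks, Group 1 commences intervention". The Study design and setting section describes the 48 weeks as "incorporating a 12 week pre-intervention period". Groups 2 and 3 start at Times 3 and 4. On this schedule no clinic has begun the programme before Time 2.

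The ANCOVAs do not stand alone. In addition, to deal with clustering, "generalised linear mixed models with random effects will be used to analyse differences between control period and intervention period".

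**The concern.** Every clinic is due to be measured twice before anyone exercises, but the method named first uses only the older score. Time 1 lies 24 weeks before Time 3 and 36 weeks before Time 4. Time 2 lies 12 and 24 weeks before them. A single sit-to-stand count is a noisy reading of a person's usual level, and a more recent one will normally predict the outcome at least as well. Two readings together predict better than one.

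What is at stake is the width of the ANCOVA confidence intervals, and how well those analyses correct chance differences between groups of only five clinics each. The trial expects 30% attrition and tests at a Bonferroni-reduced level, so precision that comes from data already collected is worth having.

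**Working it through.** **The plan's own figure.** The Sample size calculation section gives d = 0.65, alpha 0.0125, power 0.80, a design effect of 1.25 and 30% attrition. Two-sided testing is assumed.

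- Design effect: 1 + (9.73 − 1) × 0.029 = 1.253, as stated.
- The t-based size is 55 per group, so 110 × 1.25 × 1.3 = 178.75, or 179. This agrees with 180 = 15 × 12.

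No between-visit correlation enters this calculation, so the choice of covariates does not bear on 180.

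**Inputs for the check.** The visits and their timing come from the article. The correlation between visits is not given anywhere, so it is assumed, over 0.5 to 0.9. Outcome variance is set to 1, clustering is ignored, and Time 1 and Time 2 enter as separate covariates.

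**Equal correlation r between all visits.** Residual variance is 1 − r² with Time 1 alone and 1 − 2r²/(1 + r) with both. The proportional cut simplifies to (r/(1 + r))² and is the same at Times 3 and 4.

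| r | Time 1 alone | Both | Variance cut | Standard error cut |
|---|---|---|---|---|
| 0.5 | 0.750 | 0.667 | 11% | 6% |
| 0.7 | 0.510 | 0.424 | 17% | 9% |
| 0.9 | 0.190 | 0.147 | 22% | 12% |

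**Correlation decaying with time, q per 12 weeks.** Here Time 2 carries all the information. At Time 3 the residual variance goes from 1 − q⁴ to 1 − q². At Time 4 it goes from 1 − q⁶ to 1 − q⁴.

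| q | Time 3: from, to | Variance cut | Time 4: from, to | Variance cut |
|---|---|---|---|---|
| 0.5 | 0.938, 0.750 | 20% | 0.984, 0.938 | 5% |
| 0.7 | 0.760, 0.510 | 33% | 0.882, 0.760 | 14% |
| 0.9 | 0.344, 0.190 | 45% | 0.469, 0.344 | 27% |

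The matching cuts in standard error are 11% to 26% at Time 3 and 2% to 14% at Time 4.

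**Separate covariates or their mean.** With equal correlation the two are equivalent. With decay, the mean gives weight to the older score that it does not merit. For q from 0.7 to 0.9 the cut falls to 23% to 33% at Time 3 and 10% to 20% at Time 4, so separate covariates are the better form.

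**Illustration as a detectable effect.** Take 180 × 0.70 = 126 completers, or 8.4 per clinic. Five clinics against ten is then 42 v 84. The design effect is 1 + (8.4 − 1) × 0.029 = 1.215. At two-sided alpha 0.0167 and power 0.80 the multiplier is 2.394 + 0.842 = 3.236. With equal correlation 0.7:

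- Time 1 alone: 3.236 × √[1.215 × (1/42 + 1/84) × 0.510] = 0.48 SD
- Both: 3.236 × √[1.215 × (1/42 + 1/84) × 0.424] = 0.44 SD

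This applies the same design effect to the adjusted residuals, so it shrinks the between-clinic part as well. It is an illustration, not an estimate.

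Time 5 is left out. All three groups have been exposed by then, so what an ANCOVA estimates at that visit is a separate question.

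**The case against.** The strongest reply is that nothing here is wrong. ANCOVA on one pre-exposure score is a valid, unbiased analysis, and an article may leave the exact covariate list to a fuller document. The first part stands: this is about efficiency only. The second stands in part. If the full plan already takes baseline scores to mean both visits, a clarifying sentence settles the matter. But the article does fix a meaning of baseline, and it is Time 1.

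The second reply is that the mixed model covers this. A reader might infer from the ANCOVA wording that Time 2 is discarded. The documents do not support that: in the comparison of control with intervention periods, Time 2 is a control-period observation in all 15 clinics. That model also handles clustering, so it is the better basis for inference. What remains is that the ANCOVAs are the initial method, with the mixed model added, and any ANCOVA result reported would rest on the older score alone.

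The third reply is that Time 1 is the safer covariate. Time 2 coincides with Group 1's start, and "the participants and clinic staff will be made aware of their group at the commencement of the intervention". No section states that the Time 2 test comes first. An effort-dependent score taken after disclosure could already differ between groups, and adjusting for it could distort the effect. The primary outcome is measured "by an AEP who is blinded to the intervention group", but that does not blind participants. Testing is scheduled before the midweek dialysis treatment and exercise takes place during dialysis, so a test precedes that day's session. It need not precede a session earlier in the same week. The doubt is therefore small but real, and a reader who infers that Time 1 alone wastes precision with no trade-off goes further than the text allows.

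**Conclusion.** The point holds as a modest efficiency suggestion for the ANCOVAs at Times 3 and 4. Read with the Data collection section, those analyses use Time 1 alone and pass over a measurement scheduled before any exposure and 12 weeks nearer each outcome.

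The size cannot be fixed from the documents. It spans 5% to 45% of individual-level residual variance across the patterns and visits examined, and 11% to 22% under equal correlation. The upper end needs pure decay, a high correlation and the Time 3 visit, so it should not be quoted alone. Pure decay also allows for no test-day noise, which is one of the reasons for wanting a second reading.

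A reader might infer bias, or a trial left short of power. Neither follows: the single-covariate ANCOVA is unbiased on this point, and the planned 180 assumes no gain from baseline adjustment.

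**What to change.** In the Statistical analyses section, name the Time 1 and Time 2 scores as separate covariates in the ANCOVAs of Times 3 and 4. State in advance what is done when a Time 2 score is missing, for example filling it from the Time 1 score by a regression fitted across all clinics without regard to group. In the Data collection section, state that Time 2 testing is completed before groups are disclosed and before the first exercise session in Group 1. The mixed model needs no change on this account. If baseline scores is already meant to cover both visits, saying so is enough.

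The cost is a few sentences, with no new visit, test or participant. The small downsides are the handling of missing Time 2 scores and reliance on the stated ordering being kept. If that ordering cannot be assured, keeping Time 1 alone is defensible.

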## Discussion and conclusion

The primary outcome for this study is to examine the effect of an AEP-coordinated resistance exercise intervention on hemodialysis patients’ physical function. A secondary associated outcome is the cost utility of exercise physiologists together with community activity involvement, dialysis exercise adequacy, falls and falls confidence, medication use, biochemical measures and morbidity. The importance of these measures is significant given the paucity of uptake of exercise in hemodialysis clinics worldwide. Exercise physiologists have increasingly been involved in the improved outcomes of people with chronic conditions; however, this has not been tested in the hemodialysis population. This study will provide an improved understanding on the impact of an AEP-co-ordinated resistance exercise intervention and whether it is a cost effective model for health services providing hemodialysis.
